### Sample size

Previous studies demonstrated that third-wave cognitive behavioral therapy (CBT) [22, 99, 100], including CBT focusing on self-esteem [51, 101], may lead to reductions in symptoms of psychopathology of moderate to large effect size. In line with previous research, the power calculation is based on the primary outcome of level of self-esteem as measured with the RSES [51]. Power simulation in the R environment indicated that a sample size of 130 participants (65 per condition) is sufficient to test our primary hypothesis of the effect of condition (SELFIE + TAU vs. TAU) on self-esteem, while controlling for self-esteem at baseline. Specifically, this will allow us to detect an effect size (standardized mean difference (SMD)) of 0.3 (experimental vs. control condition), i.e., a difference that is considered clinically relevant, at (at least) post-intervention or 6-month follow-up with a power of 0.87 (primary hypothesis), and, at long term, (at least) at one of the post-intervention and follow-up time points (6-month, 18-month, and 24-month follow-up), with a power of 0.82 when testing at alpha = 0.05 using linear mixed modeling. Based on our previous and ongoing work, we will allow for a 25% attrition rate at 2-year follow-up, which will result in a loss to follow-up of around 22 individuals per condition on average (see Fig. 1). Hence, we will recruit a total sample of 174 participants (87 experimental, 87 control condition) at baseline.

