### Statistical analysis

A full statistical analysis plan will be written and published prior to unblinding of the study and before any analysis is being undertaken. The trial data set will be accessed by the investigators to test the primary hypothesis of an improvement in self-esteem at post-intervention and 6-month follow-up in a priori planned statistical analysis when data collection for assessments at 6-month follow-up has been completed while retaining masking of assessors until the last assessment of the last participant at 24-month follow-up. We will use a linear regression model with the primary outcome of self-esteem at post-intervention and 6-month follow-up entered as the dependent variable and self-esteem measured at baseline, condition (SELFIE + TAU vs. TAU), time (as a two-level factor), center (as a four-level factor), the baseline × time interaction, and a time × condition interaction term as independent variables, in line with the intention-to-treat principle. All randomized participants will be included in the analysis and will be analyzed according to the intention to treat principle. Residuals within subjects will be allowed to be correlated with a completely unstructured variance-covariance matrix to take within-subject clustering of repeated measures into account. We will fit the model using Restricted Maximum Likelihood (REML [102]) in Stata 15 [103], which allows for all available data to be used assuming that data is missing at random if all variables associated with missing values are included in the model [104, 105]. Therefore, potential bias due to attrition over the study period, differences between centers, or as a function of baseline self-esteem will be minimized by the model. We will make every effort to assess all participants at post-intervention and follow-up. To test the main effect of condition, an omnibus test of no difference between the two conditions at all two time points (Wald-type test with df = 2 and alpha = .05) will be used. The two time-specific contrasts will be examined if the omnibus test is statistically significant to determine at which time points significant differences are present (each tested at alpha = .05). The two time-specific contrasts (to determine at which time points significant differences are present) will only be examined if the omnibus test is significant and, hence, the family-wise type I error rate of finding at least one significant difference at the three time points is controlled at alpha = .05. Hypotheses in relation to secondary outcomes of momentary self-esteem, positive and negative schematic beliefs of self, resilience, emotional well-being, general psychopathology, functioning, and quality of life at post-intervention and 6-month follow-up will be tested following the same steps. The investigators will access the trial data set to test hypotheses in relation to all four time points (i.e., post-intervention, 6-month, 18-month, and 24-month follow-up) in a priori planned statistical analysis when data collection for assessments at 24-month follow-up has been completed. For hypotheses in relation to primary and secondary outcomes at all four time points (i.e., post-intervention, 6-month, 18-month, and 24-month follow-up), the main effect of condition will be tested using, again, an omnibus test of no difference between the two groups at all four time points (Wald-type test with df = 4 and alpha = .05). The four time-specific contrasts will be examined to determine at which time points significant differences are present (each tested at alpha = .05), if the omnibus test shows to be statistically significant. Since randomization will be performed in blocks, stratified by region of collaborating center or as external admission, all analyses will include this as a covariate, even though it is not expected this variable will lead to bias. As participants will be randomly assigned to experimental and control condition, no differences across conditions are expected in other study parameters (socio-demographics, alcohol and substance use, medication use, treatment classification, social support and self-compassion). If, however, in contrast to what would be expected, there are significant differences at baseline in any of these parameters across conditions, these will be included as covariate(s) in analyses with primary and secondary outcomes as dependent variable. As ESM data have a multilevel structure, multiple ESM observations (level 1) will be treated as nested within time points (i.e., baseline, post-intervention and 6-month, 18-month, and 24-month follow-up) (level 2) and time points will be treated as nested within subjects (level 3).

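### The 24-month analysis tests four time-specific contrasts at 0.05 behind one df = 4 omnibus test, which controls the family-wise error only when no time point has a real effect

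*Protocol article*

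**What the plan says.** All of the relevant text is in the Statistical analysis section of the protocol article.

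- **Primary analysis (post-intervention and 6 months).** The gate is "an omnibus test of no difference between the two conditions at all two time points (Wald-type test with df = 2 and alpha = .05". The two contrasts, each at 0.05, are examined only if that test is significant. From this the protocol concludes that "the family-wise type I error rate of finding at least one significant difference at the three time points is controlled at alpha = .05".
- **24-month analysis (post-intervention, 6, 18 and 24 months).** The gate is "an omnibus test of no difference between the two groups at all four time points (Wald-type test with df = 4 and alpha = .05". The next step is "The four time-specific contrasts will be examined to determine at which time points significant differences are present (each tested at alpha = .05", on the condition "if the omnibus test shows to be statistically significant". The scheme covers primary and secondary outcomes. No other multiplicity step is given, and the statement of family-wise control is not repeated.

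**The concern.** An omnibus gate followed by unadjusted contrasts is a closed test when there are two contrasts. If one null hypothesis is false, only one true null remains, and it is tested at 0.05. With four contrasts this no longer holds: a real effect at one time point can open the gate and leave three true nulls, each tested at 0.05 with no further protection.

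The third objective and H3 ask whether effects last to 18 and 24 months. If benefit were present early and absent later, the early effects could open the gate for the late contrasts. The gate then gives little protection against a false late difference, and that is the case in which protection is needed.

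**Working it through.** **Inputs from the protocol.** A df = 2 gate with two contrasts, and a df = 4 gate with four contrasts, every test at 0.05 (Statistical analysis). Sample size section: "a sample size of 130 participants (65 per condition) is sufficient to test our primary hypothesis", and a target to "detect an effect size (standardized mean difference (SMD)) of 0.3 (experimental vs. control condition".

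**Assumptions.** Contrasts are two-sided, since sidedness is not stated. The covariance is unstructured and no correlation is given, so the time-specific z-statistics are taken as multivariate normal with equal correlation from 0 to 0.8. Each setting has 400,000 simulated draws: a chi-square omnibus at 5%, then |z| > 1.96 at the time points with no effect.

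**Step 1: the plan's own figure (two contrasts).** With none or one real effect (z-shift 0 to 8), the simulated family-wise error is 3.6% to 5.1%, that is, at most 5% within simulation error. The stated 0.05 reproduces.

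**Step 2: four contrasts.** Once the gate is certain to be open and m true nulls remain, independent estimates give 1 − 0.95^m:

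- m = 3: 1 − 0.95³ = 14.3%
- m = 2: 1 − 0.95² = 9.75%
- m = 1: 5%

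Correlation lowers the first two figures. Family-wise error with large real effects (first row: no real effect):

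| Real effects | corr. 0 | 0.3 | 0.5 | 0.7 | 0.8 |
|---|---|---|---|---|---|
| none | 4.8% | 4.5% | 3.9% | 3.3% | 2.9% |
| one | 14.3% | 13.6% | 12.5% | 10.9% | 9.8% |
| two | 9.8% | 9.5% | 9.1% | 8.3% | 7.8% |
| three | 5.0% | 5.0% | 5.0% | 5.0% | 5.0% |

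**Step 3: the planning effect.** Take SMD 0.3 at one time point only, 65 per arm, with the same correlation r between baseline and each follow-up and between follow-ups. The baseline-adjusted variance is 1 − r², so the z-shift is 0.3 / √(2(1 − r²)/65), and the correlation between adjusted estimates is r/(1 + r).

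- r = 0.3: z-shift 1.79, family-wise error 9.1%
- r = 0.5: z-shift 0.3/√(0.75 × 2/65) = 1.97, family-wise error 9.9%
- r = 0.7: z-shift 2.39, family-wise error 11.5%
- r = 0.8: z-shift 2.85, family-wise error 12.4%

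The inflation therefore does not depend on an unrealistically large effect.

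**Step 4: the wording slip.** The family-wise sentence refers to three time points, but the planned analyses have two and four. Applied to three separate contrasts, the same gate would allow up to 1 − 0.95² = 9.75%. The guarantee is true for two contrasts and would be false for three.

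**Step 5: with the fix.** Holm across the four contrasts behind the df = 4 gate, with correlation 0, 0.5 or 0.7 and a z-shift of 0, 3 or 8 at one time point, gives 2.1% to 4.9%.

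**The case against.** - **The late analysis is secondary.** The Secondary outcomes section places the 18- and 24-month RSES comparisons under H3. An omnibus gate before unadjusted contrasts is a recognised protected procedure, and strong control within a secondary family is not universally required. This limits the weight of the point. It does not remove it: the rule is fixed explicitly, and the protocol justifies its two-contrast gate by family-wise control.
- **10% to 14% is the worst configuration.** It needs a real effect at exactly one time point and none at the other three. With two real effects the error is about 8% to 10%, and with three it is 5%. A partly faded effect is still an effect, so detecting it is no type I error. This stands.
- **A reader might infer that the plan would often produce a false claim of lasting benefit.** The documents do not support that. The long-term objective covers 18 and 24 months only; the 6-month effect belongs to the first objective and is tested in the controlled df = 2 analysis. With an effect at post-intervention alone (z-shift 2 or more), a false difference at 18 or 24 months arises in 6.7% to 9.7% of trials, and one that favours SELFIE in 3.4% to 4.9%. Nor does the protocol predict an early effect that fades; it asks whether effects hold.
- **A reader might also infer that the protocol falsely claims control for the four contrasts.** It does not. The family-wise sentence concerns the two contrasts and comes before the df = 4 text. There it is right, apart from one word.

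**Conclusion.** The point holds in a limited form. The four-contrast step has weak family-wise control only. For a given outcome, the chance of at least one false time-specific finding is about 10% to 14% when one time point has a clear real effect. It is about 9% to 12% at the planning effect of SMD 0.3, about 8% to 10% when post-intervention and 6 months have real effects and the later times none, and 5% with three real effects. These figures rest on assumed equal correlations, normal z-statistics and two-sided tests. The direction of the result does not depend on the correlation chosen; the size does.

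The primary two-time-point conclusion is untouched. What is exposed is the statement of which time points differ in the 24-month analysis. This is a cheap improvement, not a flaw in the main test.

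**What to change.** Keep the df = 4 omnibus test and replace the four unadjusted contrasts by one of these:

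- **Holm across the four contrasts**, with the smallest p-value compared with 0.05/4 = 0.0125, the next with 0.05/3, and so on.
- **Closed testing**: a contrast is declared significant only if every Wald test of a subset of time points that contains it is significant at 0.05. Four time points give 15 subsets. The omnibus and the four single contrasts are already planned, so 15 − 5 = 10 further Wald tests from the same fitted model are needed.

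In the family-wise sentence, change *three* time points to *two*.

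No new data or change of design is needed, and the omnibus tests and their power stay as they are. The cost is slightly lower power for single long-term contrasts. The full analysis plan that the protocol promises before unblinding is the natural place for the change.

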#### Other measures

A socio-demographic schedule will be used to assess basic socio-demographic and clinical characteristics including age, gender, employment status, and level of education. Resilience will be assessed with the Temperament and Characteristics Inventory (TCI) [97]. Last, other confounders, such as alcohol and substance use (Composite International Diagnostic Interview (CIDI), sections B, J, and L) [98], medication use, treatment classification, and social support (Childhood Experience of Care and Abuse (CECA), section social support) [67], will also be assessed.

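### Beyond baseline RSES and center, covariates enter the primary and secondary models according to baseline significance tests, so chance imbalance, not prognostic value, settles the final model

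*Protocol article*

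**What the plan says.** All of this is in the protocol article.

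- **Terms always in the model** (Statistical analysis). These include "self-esteem measured at baseline, condition (SELFIE + TAU vs. TAU), time (as a two-level factor), center (as a four-level factor), the baseline × time interaction". The section adds that, because randomization is "stratified by region of collaborating center or as external admission, all analyses will include this as a covariate".
- **Terms that depend on a test** (Statistical analysis). The remaining parameters are "socio-demographics, alcohol and substance use, medication use, treatment classification, social support and self-compassion". The rule for them is triggered by a test and reads: "significant differences at baseline in any of these parameters across conditions, these will be included as covariate(s) in analyses with primary and secondary outcomes".
- **The article's own premise** (same place): "As participants will be randomly assigned to experimental and control condition, no differences across conditions are expected in other study parameters".
- **Where these variables come from** (Other measures). The socio-demographic schedule covers "basic socio-demographic and clinical characteristics including age, gender, employment status, and level of education", and the section then turns to "other confounders, such as alcohol and substance use".

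The rule is mandatory, applies to the primary analysis and is not labelled a sensitivity analysis. It gives neither a significance level for the baseline tests nor a prognostic criterion.

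**The concern.** Participants are randomized after the baseline assessment. If randomization is sound, the null hypothesis of no baseline difference is true by design, and a significant result says only that chance produced an imbalance. The article accepts this premise and then lets such a result change the primary model.

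Three things follow.

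- Significance of an imbalance says nothing about whether the variable predicts RSES. A variable unrelated to RSES can enter. A strong predictor stays out about 95% of the time when tested at 0.05.
- The covariate set of the primary model cannot be named until the arms have been compared. A SAP published before unblinding could repeat the rule but could not state the model.
- The power simulation in Sample size controls for baseline self-esteem and mentions none of these other variables, so a triggered model is not the one described as powered. The missing-at-random argument asks for variables associated with missingness to be in the model, and selection on imbalance does not serve that purpose.

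**Working it through.** **The plan's own figure.** The point disputes no stated number. The sample size reproduces: 65 / (1 − 0.25) = 86.67, so 87 per arm and 174 in total. The stated power of 0.87 cannot be checked directly because no correlation is given. A 2-df omnibus test with 65 per arm, SMD 0.3 at both time points and all correlations equal gives 0.73 at a correlation of 0.7 and 0.86 at 0.8, so 0.87 is attainable near 0.8.

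**How many tests.** The article names six groups of parameters. Socio-demographics contains at least four variables (age, gender, employment status, education), so 4 + 5 = 9 tests, or 10 if alcohol and substance use are tested separately.

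**Chance of at least one trigger.** With k independent tests at an assumed level of 0.05, the probability is 1 − 0.95^k:

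- k = 6: 1 − 0.95^6 = 0.265
- k = 9: 1 − 0.95^9 = 0.370 (37% in simulation)
- k = 10: 1 − 0.95^10 = 0.401

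Correlated variables trigger less often: nine tests with an assumed correlation of 0.3 give 33%.

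**What the rule does to power and level.** Simulation with 65 per arm, one time point, an assumed baseline correlation of 0.7, nine independent covariates and SMD 0.3. The power levels below are for this simplified setting and should be compared with each other, not with 0.87.

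| Assumed partial correlation with the baseline-adjusted outcome | No extra covariates | Baseline-test rule | All nine fixed |
|---|---|---|---|
| 0 for all nine: power | 0.64 | 0.64 | 0.62 |
| 0.2 for all nine: power | 0.66 | 0.67 | 0.81 |
| 0.2 for all nine: type I error | 0.045 | 0.037 | 0.050 |

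The 0.2 rows are generous, since nine such covariates explain 9 × 0.2² = 36% of the residual variance. In milder settings, type I error is 0.048 under the rule against 0.050 without extra covariates (one covariate at 0.3), and 0.054 against 0.053 (two at 0.2), with Monte Carlo standard error about 0.0025. Power in settings with one or two prognostic covariates is 0.65 to 0.66 with or without the rule, and 0.68 to 0.70 when those covariates are fixed in the model.

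**What a fixed prognostic covariate is worth.** The gain in effective sample size is 1/(1 − r²) − 1, where r is the partial correlation with the outcome after baseline adjustment. The article gives no value for r, so a range is shown:

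- r = 0.1: 1/0.99 − 1 = 1%
- r = 0.2: 1/0.96 − 1 = 4%
- r = 0.3: 1/0.91 − 1 = 10%
- r = 0.4: 1/0.84 − 1 = 19%

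**The case against.** The best defence is that the rule is stated in advance, uses baseline data and allocation but no outcomes, and touches only secondary predictors. The baseline outcome measure, usually the strongest predictor, is already fixed, as is the stratification factor. The tests could be run on coded arms, in keeping with the blind analysis described in Study design. Adjusting for an observed imbalance in a prognostic variable is also sensible in itself.

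Much of this stands, and it limits the harm. But the distortion from an imbalance depends on its size and on prognostic strength together, and the rule looks only at the first. With 87 per arm, a continuous variable reaches significance at about 1.96 × √(2/87) = 0.30 SD. A strong predictor out of balance by slightly less is ignored, while an irrelevant variable just above that is added. Fixed adjustment for a predictor deals with its imbalance whatever its size. Coding the arms does not help either, because the model still depends on comparing them.

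Three stronger readings are tempting but not supported.

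- *A reader might infer that the rule inflates type I error.* The simulations show a level that is nominal or slightly conservative.
- *A reader might infer that the rule itself costs precision.* A model with only baseline RSES and stratum forgoes the same precision. The rule merely fails to gain it, and the size of that gain rests on correlations the article does not give.
- *A reader might infer that self-compassion, listed in "treatment classification, social support and self-compassion", has no measure.* The assessment schedule (Fig. 2) is not shown and the list in Other measures is open, so its absence from the visible text proves nothing.

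**Conclusion.** The concern holds for the covariates beyond baseline RSES, its time interaction and the center or stratum. The article states a rule that lets chance imbalance settle which of them enter the primary and secondary models. Chance alone would change the model in roughly a quarter to two-fifths of correctly randomized trials (26% to 40% for 6 to 10 tests). That range assumes independent tests at 0.05; correlation lowers it, to 33% for nine tests in the example.

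The consequence is a primary model not fully fixed in advance, and a rule that buys almost no power. The numerical damage is modest and the validity of the primary test is not in doubt. Because this is a stated rule and not a detail left to the SAP, it should be corrected.

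**What to change.** - Delete the baseline-test rule.
- Before unblinding, fix the primary covariates as baseline RSES with its time interaction and the four-level stratum. Optionally add one or two variables already collected, chosen in advance for their expected relation to RSES.
- Report baseline characteristics by arm without significance tests.
- Put any further adjustment in one prespecified sensitivity model.

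The cost is wording in the protocol and SAP. No new data are needed and 174 does not change. The downside is a small loss of degrees of freedom if an added covariate proves non-prognostic. Even nine useless covariates lowered simulated power only from 0.64 to 0.62, so one or two would cost very little.

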#### Interim analyses and stopping guidelines

Since it is not expected that any harm will occur related to participation in this study, there are no predefined stopping guidelines and no a priori planned interim analyses. The DMEC can recommend to the Coordinator and TSC for interim analyses to be conducted if deemed necessary because of any ethical or safety concerns.

### Research governance

Maastricht University is the sponsor of this study. The trial has received ethical approval from the Medical Ethics Review Committee (MERC) at Maastricht University Medical Centre (MUMC), the Netherlands (reference: NL64393.068.17). Amendments to the study protocol will be submitted to the MERC for approval, then communicated to all relevant parties (DMEC, TSC, the sponsor, funder, and collaborating centers) and will be updated in the clinical trial registry. In case of deviations from the study protocol, a breach report form will be used for documentation. The handling of the data will be in compliance with the Dutch and European General Data Protection Regulation (GDPR). If a participant withdraws their consent, all data from that participant will be destroyed. No biological specimens will be collected in this trial. All data will be handled confidentially and will be coded using a number according the order of entry. In line with the GDPR, all data will be securely stored and personal data will be stored separately from the number-coded data. Consistent with the consortium agreement of this study, the coordinator will have overall responsibility for the trial and will be responsible for the day-to-day management of the project. The project leader advices on, and supports, the coordinator in the day-to-day management of the project. Each party (i.e., School for Mental Health and Neuroscience, Mondriaan, Levvel, Academic Medical Centre Amsterdam, Parnassia) appoints its lead scientist on the project as principal investigator (PI). The coordinator and project leader will liaise closely with all PIs on recruitment and consent procedures. The Trial Management Committee will meet monthly and includes the coordinator, the project leader and all PIs. It will be chaired by the coordinator and will manage the day-to-day running of the study, audit the trial conduct, and oversee preparation of reports to the MERC, the TSC, and the DMEC. The coordinator will permit trial-related monitoring, audits, and MERC review (conducted by the Clinical Trial Center Maastricht, which is independent from the study sponsor (i.e., Maastricht University)). The TSC will meet at least annually to provide independent overall supervision of the trial, to approve the protocol and any amendments and to monitor progress (e.g., data completion rates and adherence to the protocol). Also, the DMEC will meet at least annually. The DMEC will advise on ethical or safety concerns and, for the experimental condition, monitor evidence for intervention harm (e.g., SAEs) and review whether these events are in line with expectations. The DMEC can recommend to the coordinator and TSC to be given access to all trial data as well for interim analyses to be conducted and the trial to be terminated prematurely if deemed necessary.
